### Patient follow‐up

2.6

Blood collection for serum chemistry, hematology, coagulation, and batch analysis of proteins involved in the process of calcification such as MGP and Fetuin‐A are measured at 1 Week, 1, 3, 6, 9, 12, and 24 months. Echocardiography was performed at baseline, 6, 9, 12, and 24 months (evaluation by an experienced echocardiographer with at least 10 years' experience). Calcification score (coronary or valvular) as assessed by cardiac CT was measured at 12 and 24 months. To improve clinical consistency, all CT scans were evaluated in a consensus reading by an experienced radiologist and an experienced cardiologist. Measurement of changes in intima‐media thickness of carotid artery (IMT) and flow‐mediated vasodilation of brachial artery (FMD) are performed at baseline, 6, 12, and 24 months. Blood pressure was measured at 1 week and at 1, 6, 9, 12, and 24 months. Electrocardiography was performed at 12 and 24 months. Adverse Events were evaluated at 1 week, 1, 6, 9, 12, and 24 months. MACE and major and nonmajor bleedings are documented at every visit.

The study duration was approximately 6.5 years. The planned duration of study inclusion was 55 months; the follow‐up period is 24 months. According to the trial design patients were followed‐up at 1 week as well as 1, 3, 6, 9, 12, and 24 months after inclusion.

The design of the study is illustrated in Figure 1.

**Figure 1 clc23819-fig-0001:**
[figure not shown]
Trial design

### Cardiac calcification assessment with CT‐scanning

2.7

The progression of valvular and coronary calcification will be assessed by cardiac CT. Valvular calcifications, representatively measured by aortic valve calcification, will be quantified by aortic valve calcium scoring (AVCS), coronary calcifications will be quantified by coronary calcium scoring (CAC), using the AS for CAC and an Agatston‐equivalent score for AVCS, the volume score (expressed as millimeter cubic) and the mass score (expressed as milligram calcium hydroxyapatite), respectively. A previous large interventional trial (ADVANCE) in hemodialysis patients revealed differences in calcification development quantification depending upon the specific score applied.^19^ Thus, the reliability of calcification assessment by each of these three scores needs to be discussed. In summary, the volume calcification score is regarded as superior (most reliable) to the others. AS reliability is sensitive to image noise and slice thickness, which lowers the reproducibility of this method. Furthermore, AS is a virtual value and does not represent a physical value. Although the concept of mass score theoretically seems to be more robust and reliable than volume score and AS,^20^ its calculation is challenging, and hence, the mass score is usually not used in international multicenter trial.^21^ Volume score is less sensitive to image noise, or in other words, to the patient's habitus. Therefore, measurements of the volume score are more reliable and robust,^19^ which goes in line with, for example, the results of the MESA cohort.^22^ Overall, the present study will assess Agatston and volume scores in parallel and therefore provide results of a clinically frequently applied and established score (AS) and a reliable, stable score (volume) at the same time.

### MSCT

2.8

For calcium scoring, noncontrast ECG‐triggered MSCT of the whole heart was performed in a step‐and‐shoot‐technique, as generally accepted and recommended by current guidelines. Scan length is defined by a scout view from the tracheal bifurcation to the bottom of the heart silhouette. CT scanners at the different study sites are at least 64‐slice MSCT scanners dedicated to cardiac imaging (SOMATOM Definition Flash and Aquilion Prime, Canon Medical Systems). To achieve reproducible and comparable calcium scoring results, every scanner is separately calibrated with a dedicated calcium calibration phantom (Anthropomorphic Cardio CT Phantom, size 300 × 200 × 100 mm, QRM Quality Assurance in Radiology and Medicine GmbH). The same basic scan parameters (e.g., 80 mAs, 120 kV, 3/0.75 mm slice thickness, same rotation time, same collimation, same pitch) are used at all sites and if necessary, are adapted to each participant's individual physique. Afterward, CT scans are transferred to a dedicated postprocessing and measurement workstation (SyngoCaScoring, Wizard; Siemens) for quantification of valvular and coronary calcifications. Both, valvular and coronary calcification measurements are performed using a dedicated software tool (Syngo MMWP, VA13A; Siemens). The volume score is determined by the calculated volume (Hounsfield units > 130 and a minimum size of 0.5 mm^3^) based on isotropic interpolation.^23^ The AS is calculated by multiplying the density and size of the calcified areas as previously described.^24^ According to the above‐listed exclusion criteria, patients with extensive, multivessel coronary stents, which make coronary artery calcification scoring impossible or unreliable, are excluded by study design. In patients with single‐vessel stenting, a CAC is carefully done with manual exclusion of the stent, if technically possible. In case of technical impossibility of CAC measurement, patients are excluded from further study participation.

The core cardiology is located at the RWTH University Hospital radiology department. All measurements are performed by the same radiologist with more than 10 years of experience in calculating and interpreting calcium deposits in coronary arteries and heart valves. The radiologist is blinded to the patients' individual history, treatment randomization, and the date of the examination. To improve intra‐reader reproducibility, baseline and follow‐up CT are presented to the reader immediately following each other in random order.

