### STUDY OBJECTIVES

2.2

*The primary endpoint* is the *p*rogression of coronary and aortic valve calcification (quantified by the calcification volume score) as assessed by cardiac computed tomography (CT) at 24 months. The secondary objectives can be found in the Supporting Information Material.

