### Statistical analysis

2.9

All randomized patients with OAT due to atrial fibrillation or atrial fibrillation and/or pulmonary embolism are included in the analyses. Descriptive analyses of study data include frequencies, mean, standard deviation median, minimum, maximum values, and frequencies of missing data. Furthermore, a description of the change from baseline (absolute difference and percentage change) will be given. The calcification volume score is used in the primary analysis to evaluate the treatment effect. A linear mixed‐effects model is used with treatment effect, visit, baseline measurement, and treatment‐visit interactions as fixed effects and random intercepts for participants are included. For the primary inferential analysis, the hypothesis that the treatment‐visit interaction parameters are jointly equal to zero is tested using an *F *test. Additionally, 95% confidence intervals of parameter estimates are presented. In secondary analyses, the valvular and aortic calcification endpoints are analyzed using similar mixed models as in the primary analysis. An interim analysis is planned after 12 months of follow‐up. Significance levels are adjusted using the Fleming‐Harrington‐O'Brien method. A 5% overall significance level is used in the primary analysis. All statistical analyses are conducted using SAS or SPSS.

For the calculation of sample size for detecting the difference in volume score change between the two treatment groups the standard deviation of the change in volume, score was assumed to be 234 units, based on previous data measuring volume score change over 12 months in placebo‐treated patients with asymptomatic or mildly symptomatic aortic valve calcification.^20^ Given this assumption on the variability of volume score change, a sample size of 95 per treatment group (*n* = 190 altogether) would allow a detection of 96 units difference between the treatment groups with an 80% power using a Type 1 error of 0.05.

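### The rule that removes patients whose coronary score cannot be measured is not confined to screening, and stent masking is not required to match across a patient's scans

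*Protocol article*

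**What the plan says.** Three rules stand together in section 2.8 (MSCT) of the protocol article:

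- Patients with extensive multivessel stents, "which make coronary artery calcification scoring impossible or unreliable, are excluded by study design".
- With single-vessel stenting, "a CAC is carefully done with manual exclusion of the stent, if technically possible".
- Finally: "In case of technical impossibility of CAC measurement, patients are excluded from further study participation".

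None of the three gives a time point. The second does not separate stents present at baseline from stents placed later. The closing paragraph of the section says that a single blinded radiologist reads a patient's baseline and follow-up scans one after the other, in random order.

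Section 2.9 (Statistical analysis) defines the analysis population: "All randomized patients with OAT due to atrial fibrillation or atrial fibrillation and/or pulmonary embolism are included in the analyses". For the primary analysis, "A linear mixed‐effects model is used with treatment effect, visit, baseline measurement, and treatment‐visit interactions as fixed effects", plus random intercepts for participants.

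Section 2.2 (Study objectives) makes both coronary and aortic valve calcification at 24 months the primary endpoint. Section 2.4 admits patients on valvular calcification alone. Section 2.6 records MACE and bleeding at every visit.

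**The concern.** If the removal rule is applied after randomisation, a patient leaves the trial because of the state of the organ being measured. Three things are then at stake.

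- **Population.** Patients removed in this way cannot contribute fully to an analysis of everyone randomised. If baseline enters the model only as a covariate, a patient removed before the 12-month scan contributes no coronary response at all.
- **Other outcomes.** The valve score, MACE and bleeding remain measurable when the coronary score is not. A patient enrolled for valve calcification alone could be lost because of a coronary measurement.
- **Measurement.** If a segment is stented during follow-up and masked only on the later scan, its calcium counts at baseline but not afterwards, and the change score falls for a reason unrelated to biology.

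The question has practical weight here. Table 1 reports coronary heart disease in 54.8% of the phenprocoumon group and 60.6% of the rivaroxaban group, so stents may not be rare. These are baseline figures, however, and give no rate of new stents.

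**Working it through.** **1. Does the wording reach beyond screening?**

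Stents that prevent scoring at entry are already dealt with by the first rule. The third rule uses different words, speaks of further participation and gives no time limit. It stands in the section that describes the measurement of all scans. Against this, it follows directly on a reference to the exclusion criteria, and a screening CT is required for entry (section 2.4). Both readings are open.

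**2. What follows from each reading?**

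| Reading | Section 2.9, all randomised analysed | Valve, MACE and bleeding data |
|---|---|---|
| Screening only | No conflict | Nothing lost after randomisation |
| Also after randomisation | Conflict | Collection ends although still measurable |

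**3. The plan's own figure.**

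Inputs from section 2.9: SD 234, difference 96, 80% power, type 1 error 0.05 (taken as two-sided).

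n per arm = 2 × (1.960 + 0.842)² × 234² / 96² = 2 × 7.85 × 54,756 / 9,216 ≈ 93.3, so 94.

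The plan states 95, at which power is 0.807 (0.803 with the t distribution). The figure is reproduced and is not in dispute. It serves only as the scale for what follows.

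**4. Illustration of outcome-dependent removal.**

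The documents give no removal rate, so these fractions are assumptions. Simulated changes are normal with SD 234 and a true difference of 96. Patients above a common upper cut-off are removed from both arms.

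| Top fraction removed (pooled) | Removed, slower arm / faster arm | Difference left | Power, starting from 95 per arm | Difference if only half above the cut-off are removed |
|---|---|---|---|---|
| 2% | 1.1% / 2.9% | 86.7 | 0.760 | 91.5 |
| 5% | 3.0% / 7.0% | 78.5 | 0.705 | 87.8 |
| 10% | 6.5% / 13.5% | 69.0 | 0.625 | 84.1 |

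If the same fractions were lost at random, the expected difference would stay at 96 and power would be 0.799, 0.786 and 0.767 (93, 90 and 86 per arm). The attenuation therefore comes entirely from assuming that removal tracks progression. The illustration compares single changes and ignores any 12-month scan that the mixed model would keep, so it is not a forecast.

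**5. Illustration of masking at follow-up only.**

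Bias in the difference (VKA minus rivaroxaban) = −(new-stent rate on VKA − new-stent rate on rivaroxaban) × masked baseline volume. Rates and volumes are assumptions, with volume taken as equal in the two arms.

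- 5% against 5%, any volume: 0.
- 5% against 3%, 100 to 400 units: −0.02 × 100 = −2 to −0.02 × 400 = −8.
- 8% against 4%, 100 to 400 units: −0.04 × 100 = −4 to −0.04 × 400 = −16, and 16/96 = 17% of the target difference.

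The sign reverses if new stents are more frequent on rivaroxaban. For one affected patient, 400 units would be 400/234 = 1.7 SD, but this carries into the treatment comparison only through the imbalance between arms.

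**The case against.** The strongest reply is that this is an eligibility rule. It follows the stent exclusions, randomisation comes after the criteria are checked (section 2.5), and a consented patient whose screening CT cannot be scored would naturally be barred from going further. The exclusion list is in a supplement that is not shown. On this reading there is no conflict with section 2.9 and no lost follow-up. Even on the other reading, ending participation is not the same as deleting data, and the mixed model can use scans already taken. Stents present at baseline would be masked throughout and cause no fall. Consecutive reading of a patient's scans makes matched masking easy, and a condensed article may leave that detail to the imaging manual.

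Most of this stands, and it limits the point. It does not remove it: the rule is written down without a time limit, and the sentence does not say that it stops at randomisation. Paired reading makes matched masking feasible but does not require it.

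A reader might go further and infer that the fastest progressors are being dropped, that new stents make calcification appear to fall, or that the comparison is biased towards no effect. The article supports none of these. It does not mention stents placed during follow-up, links neither stenting nor an unmeasurable score to the rate of progression, and leaves room for purely technical causes. Nor can the fall from 164 patients with data at 12 months to 91 later (section 3) be put down to this rule, since no reasons for loss are given.

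**Conclusion.** The point holds as a defect in a stated rule. As worded, section 2.8 permits removal after randomisation on the basis of the outcome measurement. Used that way, it contradicts section 2.9 and gives up valve, MACE and bleeding data for no reason of measurement. The masking rule leaves open an artificial fall in the score after a new stent.

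Neither the size nor the direction of any bias can be derived from the documents. The losses shown for removal (96 reduced to between 86.7 and 69.0) require that those removed are the upper tail of progression. The 2 to 16 units shown for masking require both unmatched masking and more new stents on VKA. With equal rates and volumes the masking bias is zero. The mixed model handles loss that depends on observed scores, but not loss that depends on the score that could not be obtained.

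**What to change.** - State in section 2.8 that the exclusion for an unmeasurable coronary score applies only at screening, before randomisation, and reconcile the sentence with section 2.9.
- After randomisation, set only the unmeasurable coronary score to missing. Keep the patient in follow-up and in the analysis with valve scores, MACE, bleeding and all earlier scans. If the primary variable combines coronary and valve scores, say what is analysed when only one is available.
- For any stent, mask the same segments on all of that patient's scans, re-reading the stored baseline scan where the stent came later.
- Report unmeasurable coronary scores, removals and new stents by arm.
- Add a sensitivity analysis that allows the missing coronary scores to differ systematically from those observed, because setting them to missing in the mixed model does not correct loss that depends on the unobserved value.

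**Cost.** This means a wording change, the re-reading of what should be a few stored scans, slightly less calcium counted in those patients, and one extra analysis. Recruitment ended in 2018 and follow-up lasts 24 months, so visits should have ended by about 2020. Any patient already removed cannot be followed prospectively. For such patients the remedy is to use what was collected, score the valve on existing scans and report the numbers.

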### Statistical analysis

2.9

All randomized patients with OAT due to atrial fibrillation or atrial fibrillation and/or pulmonary embolism are included in the analyses. Descriptive analyses of study data include frequencies, mean, standard deviation median, minimum, maximum values, and frequencies of missing data. Furthermore, a description of the change from baseline (absolute difference and percentage change) will be given. The calcification volume score is used in the primary analysis to evaluate the treatment effect. A linear mixed‐effects model is used with treatment effect, visit, baseline measurement, and treatment‐visit interactions as fixed effects and random intercepts for participants are included. For the primary inferential analysis, the hypothesis that the treatment‐visit interaction parameters are jointly equal to zero is tested using an *F *test. Additionally, 95% confidence intervals of parameter estimates are presented. In secondary analyses, the valvular and aortic calcification endpoints are analyzed using similar mixed models as in the primary analysis. An interim analysis is planned after 12 months of follow‐up. Significance levels are adjusted using the Fleming‐Harrington‐O'Brien method. A 5% overall significance level is used in the primary analysis. All statistical analyses are conducted using SAS or SPSS.

For the calculation of sample size for detecting the difference in volume score change between the two treatment groups the standard deviation of the change in volume, score was assumed to be 234 units, based on previous data measuring volume score change over 12 months in placebo‐treated patients with asymptomatic or mildly symptomatic aortic valve calcification.^20^ Given this assumption on the variability of volume score change, a sample size of 95 per treatment group (*n* = 190 altogether) would allow a detection of 96 units difference between the treatment groups with an 80% power using a Type 1 error of 0.05.

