### Conduct of the trial

2.5

After evaluation of inclusion and exclusion criteria and after written informed consent the patients were randomized to two arms (1:1):

Arm A: Rivaroxaban (tablet) with 20 mg once daily for patients with atrial fibrillation with eGFR > 49 ml per minute and 15 mg rivaroxaban once daily for patients with eGFR of 15–49 ml. Rivaroxaban (tablet) for patients with pulmonary embolism: 2× a day 15 mg at Days 1–21 and 1 × 20 mg from Day 22.

Arm B: Adjusted dose coumadin/phenprocoumon (tablet) titrated according to target INR with a target range of 2.0–3.0 according to ACC/AHA/ESC guidelines.^2^

To limit the number of study patients and to detect a sufficient progression of coronary artery or aortic valve calcification within the follow‐up period of 2 years, this study was limited to high‐risk patients defined by baseline calcium AS > 50 (either coronary or valvular).

This threshold ensures a measurable progression in outmost patients as the progression of valvular and coronary calcification is dependent on the baseline calcium load (23–25).

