## RESULTS

3

In total 192 patients were recruited between 2013 and 2018. Of these, baseline data is available for 188 patients (95 in the Phenprocoumon group and 93 in the Rivaroxaban group). The median age of the patients was 72 (IQR 67–76) in the Phenprocoumon group and 68 (IQR 65–75) in the Rivaroxaban group. Within the groups, there were 73.6% and 69.9% male patients, respectively. The main indication for anticoagulation was atrial fibrillation (95.8% and 96.8%, respectively) with pulmonary embolism being the only other indication (Table 1). In total, data for 164 patients (82 patients per group [85%]) is available at 12 months follow up and for 91 patients (45 in the Rivaroxaban group [47%] and 46 [48%] in the Phenprocoumon group). We expect the results of the study to be ready for publication by the end of 2022.

**Table 1 clc23819-tbl-0001:** Characteristics of the patients at baseline (IRIVASC)

	Phenprocoumon (*N *= 95)	Rivaroxaban (*N* = 93)
Median age (IQR), year	72 (67–76)	68 (65–75)
Male, no. (%)	70 (73.6)	65 (69.9)
Diabetes mellitus, no. (%)	23 (24.7)	26 (29.2)
Smoker, no. (%)	11 (11.5)	14 (15)
Non smoker, no. (%)	39 (41)	45 (48.3)
Ex. smoker, no. (%)	42 (44.2)	28 (30.1)
Previous MI, no. (%)	25 (26.3)	26 (27.9)
Previous stroke, no. (%)	16 (16.8)	8 (8.6)
Coronary heart disease (CHD), no. (%)	51 (54.8)	54 (60.6)
Median systolic blood pressure, right (IQR), mmHg	130 (120–143,7)	135,5 (122,7–149)
Median systolic blood pressure, left (IQR), mmHg	130 (120–140)	134 (124–145)
Median total cholesterol (IQR), mg/dl	173 (149.7–204.2)	176 (142–214.5)
Median LDL‐cholesterol (IQR), mg/dl	109 (85.5–128,5)	102.5 (82–138)
Median GFR (IQR), ml/min/1.73 m^2^	65.6 (52.8—81.5)	72.3 (57.2–84.7)
Median hemoglobin (IQR), g/dl	13.9 (13.2–15.2)	14.2 (13.1–15)
Median CHA2DS2VASc score (IQR)	3 (3–4)	3 (2–4)
Indication for anticoagulation:		
1. Atrial fibrillation, no. (%)	91 (95.8)	90 (96.8)
2. Pulmonary embolism, no. (%)	4 (4.2)	3 (3.2)
Type of atrial fibrillation		
1. Paroxysmal, no. (%)	51 (56)	57 (63.3)
2. Persistent, no. (%)	15 (16.5)	14 (15.6)
3. Permanent, no. (%)	16 (17.6)	15 (16.7)
4. New onset, no. (%)	1 (1.1)	1 (1.1)
5. Not further classified, no. (%)	8 (8.8)	3 (3.3)

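### Baseline volume score is only a main effect in the primary model, so it adds nothing to the complete-data treatment-by-visit test and may adjust the 24-month comparison incompletely

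*Protocol article*

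**What the plan says.** The Statistical analysis section of the protocol article lists the fixed effects: "A linear mixed‐effects model is used with treatment effect, visit, baseline measurement, and treatment‐visit interactions as fixed effects". It adds that "random intercepts for participants are included". For the primary inference, "the hypothesis that the treatment‐visit interaction parameters are jointly equal to zero is tested" with an F test. The list has no baseline-by-visit term.

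The endpoint is progression "as assessed by cardiac computed tomography (CT) at 24 months" (Study objectives). For post-baseline CT, the Patient follow-up section states: "Calcification score (coronary or valvular) as assessed by cardiac CT was measured at 12 and 24 months".

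In Conduct of the trial, the entry threshold is justified by the statement that "the progression of valvular and coronary calcification is dependent on the baseline calcium load".

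On follow-up, the Results section reports that "data for 164 patients (82 patients per group [85%]) is available at 12 months follow up and for 91 patients", the latter being 45 on rivaroxaban and 46 on phenprocoumon. That sentence does not name the second time point; from the context it is 24 months. No reason for the missing data is given.

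**The concern.** The design argument and the model do not match. If patients with more calcium at entry progress faster, and go on doing so in year 2, the regression of the raw score on baseline is steeper at 24 than at 12 months. A model with one baseline coefficient forces the two slopes to be equal.

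Two things are at stake. The first is precision: baseline is likely to be a strong predictor of later score, yet as a main effect it cannot sharpen a test built on within-patient change between visits. The second is protection against missing data. Roughly half of the patients lack the endpoint visit, and a likelihood-based mixed model corrects for baseline-related loss only as far as its baseline terms are correctly specified.

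**Working it through.** **The plan's own figure.** With SD 234, difference 96, 80% power and alpha 0.05 (two-sided assumed), n per arm = 2 × (1.960 + 0.842)² × 234² / 96² ≈ 93.3, so 94. The noncentral-t version gives 95 with power 0.803. The stated 95 per group is reproduced and is not in dispute here.

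**Step 1: cancellation with complete data.** Write the planned model for patient i at visit j as

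Y_ij = β0 + β1·T_i + β2·V_j + β3·T_i·V_j + γ·B_i + u_i + e_ij.

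The 24-minus-12-month difference is D_i = β2 + β3·T_i + (e_i,24 − e_i,12). Both γ·B_i and u_i disappear, so the interaction estimate is the difference in mean D between arms, whatever γ is. One simulated complete data set (n = 188, progression 15% of baseline per year) gave:

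| Model | Interaction (SE) | SE of 24-month difference |
|---|---|---|
| No baseline | 12.56 (32.77) | 132.1 |
| Baseline main effect (as planned) | 12.56 (32.77) | 30.1 |
| Baseline-by-visit added | 12.77 (28.00) | 28.9 |

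The main effect does nothing for the interaction but a great deal for the 24-month difference. There the extra term lowers the SE only from 30.1 to 28.9, about 4%. The cancellation also holds if the baseline scan is itself counted as a visit.

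**Step 2: precision forgone in the interaction test.** With baseline-by-visit, D_i is regressed on baseline, so its residual SD is multiplied by √(1 − r²), where r is the correlation between baseline and 12-to-24-month change. The article does not give r.

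| r | √(1 − r²) | SE reduction | Equivalent extra patients, 1/(1 − r²) − 1 |
|---|---|---|---|
| 0.3 | 0.954 | 5% | 10% |
| 0.5 | 0.866 | 13% | 33% |
| 0.7 | 0.714 | 29% | 96% |

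For the 24-month contrast, with the reported counts and random loss, simulation gave an empirical SD of 62.7 falling to 58.5 at r = 0.5 (7%), and 56.9 falling to 51.0 at r = 0.7 (10%).

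**Step 3: incomplete follow-up.** From 188 patients with baseline data, 164/188 = 87% have 12-month data and 91/188 = 48% have the later data. (The article's own percentages use 96 per group.) The article reports data, not specifically CT scans; the two are assumed to coincide.

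With missing visits the model also uses between-patient information, so cancellation is no longer exact. In one simulated sample with a true effect of zero and opposite dropout dependence in the two arms, the interaction estimate was 114.5 without baseline, 97.1 with the main effect and 21.3 with baseline-by-visit.

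**Step 4: bias at 24 months under no treatment effect.** Large-sample simulation used 85% seen at 12 months and 48% at 24 months in each arm. Assumed, and not in the article: baseline mean and SD 800, residual correlation 0.6, and dropout log-odds slope 0.7 per SD of log baseline. Entries are bias in units.

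| Progression, % of baseline per year | Same dependence in both arms, as planned | One arm only, as planned | Opposite dependence, as planned | Opposite, no baseline in model | Opposite, baseline-by-visit |
|---|---|---|---|---|---|
| 5 | −1.7 | 10 | 16 | 28 | 0.3 |
| 10 | −0.5 | 16 | 31 | 45 | −0.1 |
| 15 | 0.9 | 24 | 46 | 69 | −0.5 |
| 20 | −0.8 | 32 | 59 | 79 | 1.3 |

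Values within about 2 units of zero are simulation error. If progression does not depend on baseline, the planned model shows no bias even with opposite dependence. In the opposite-dependence case the main effect removes part of the bias of the no-baseline model: (28 − 16)/28 ≈ 43% at the lowest progression rate and (79 − 59)/79 ≈ 25% at the highest.

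Null rejection of the interaction test under opposite dependence (n = 188, 500 runs) was 12% at 10% per year and 32% at 20% per year with the planned model, against 4% and 5% with baseline-by-visit. With the same dependence in both arms the planned model rejected in about 7%, where simulation error is about 1 percentage point.

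**The case against.** The case on the other side is substantial, and most of it limits the size of the point.

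- A reader might infer that baseline adjustment is useless at 24 months. It is not. The 24-month difference is the treatment effect plus the interaction, and the main effect adjusts it strongly (Step 1). Full cancellation concerns the interaction test with complete data only, and so stems partly from the choice of that contrast as primary.
- A reader might infer that the 24-month result will be biased. The article does not support this. Bias needs loss that depends on baseline calcium differently by arm. The counts are nearly identical (82 v 82, 45 v 46) and no reason for loss is given. Equal counts and an open-label design do not exclude arm-specific selection, but they are not evidence for it.
- A reader might count chance baseline imbalance as a further bias. Under randomisation it is already part of the unadjusted standard error, so it is the precision loss of Step 2 counted again.
- The steeper slope is a feature of the raw scale. If progression is proportional to baseline, log score has slope 1 on log baseline at both visits, and the term is needed less.
- The article condenses a fuller plan, which may contain the term. This stands as a caution. But the article gives an explicit list of fixed effects, and that list can be judged as written.

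**Conclusion.** The point holds in a limited form. As published, the primary model imposes one baseline slope on the 12- and 24-month raw volume scores, which conflicts with the article's own statement that progression depends on baseline load. With complete data the primary F test gains nothing from the baseline covariate; with the reported follow-up it gains only a partial adjustment.

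The precision forgone in the complete-data interaction test is about 5% to 29% of the standard error for r from 0.3 to 0.7, and less for the 24-month contrast. Bias of about 10 to 60 units at 24 months, against the 96-unit target, arises only if loss is related to baseline differently in the two arms. The article neither shows nor excludes that. Every size here depends on an assumed baseline distribution, progression rate, correlation or dropout mechanism. The cancellation itself needs no such assumption.

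**What to change.** Add a baseline volume score-by-visit interaction to the fixed effects of the primary model. Do the same, with the matching baseline score, in the parallel mixed models for the secondary calcification endpoints. Estimate the treatment difference from the amended model. If a log-scale analysis is adopted instead, put baseline on the same scale; the term then matters less but does no harm.

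The cost is one degree of freedom with visits at 12 and 24 months, and no new data. It does require a dated, documented amendment before the 24-month data are analysed. Because the trial is open-label, 12-month data are already in hand and a 12-month interim analysis was planned, the amendment should state what outcome data by arm had been seen when it was made. If the full analysis plan already contains the term, it is enough to say so in the report.
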